### Statistical analyses

Data analysis will be performed using Statistical Analysis System (SAS) software. Probability (p) of less than 0.05 will be considered significant. Experimental outcomes for continuous variables will be expressed as means ± standard deviation for each time point and the variance between the groups will be analyzed using ANOVA. Categorical variables will be compared with a chi-square test. In order to examine the relationship between variables, regression analysis will be performed. If more than one predictor variable is found to affect the outcome, multivariate regression will be employed to identify significant associations.

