## Background

It is widely recognized that pre-menopausal women are relatively protected from cardiovascular disease (CVD), including the manifestations of (*i*) coronary artery diseases (CAD, e.g., angina & heart attacks), and (*ii*) stroke. However, this advantage is lost after menopause [1–3]. In fact, one-third of all deaths in post-menopausal women are due to CAD [4], with a higher risk and overall mortality in women who experience premature or early-onset menopause [5]. As more women worldwide with hereditary breast and ovarian cancer mutations consider surgical removal of their ovaries and fallopian tubes (“prophylactic salpingo-oophorectomy”, PSO) to reduce their cancer risk, it is increasingly important to highlight the potential cardiovascular risks that accompany such an intervention and the ensuing premature, “surgical” menopause. The aim of this study will thus be to investigate whether PSO leads to increased cardiovascular risk as assessed by the measurement of conventional and novel surrogate markers for CAD. The rationale and methodology is thereby presented herein as a *study protocol* manuscript.

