### Data collection

Cardiac consultations will take place before and at 6- and 12-months after surgery, during which patients will be given an ECG and monitored for incident hypertension, diabetes mellitus, and cardiovascular events (e.g., myocardial infarction, stroke). Fasting blood and urine samples will be collected before surgery (PSO or other pelvic) and at 1, 3, 6, and 12 months after surgery. In addition to routine blood tests (glucose, hemoglobin A1c), Calgary Lab Services will conduct the following analyses: lipid profile (total cholesterol, HDL, LDL, triglycerides) and a female endocrine panel (estradiol, progesterone, FSH, LH). Our research laboratory will separately analyze blood samples at these time points for assessment of novel cardiovascular biomarkers. Plasma will be extracted from blood samples, aliquoted, and stored at -80 °C for future testing (e.g., enzyme-linked immunosorbent assays for HSP27, HSP27 antibodies, PCSK9, as well as inflammatory cytokine arrays [performed by EVE Technologies on campus]). Urine samples will also be stored at -80 °C for future isolation of microparticles and exosomes (ultracentrifugation) and detection of HSP27 and PCSK9 (Western blot and mass spectrometry). Retinal images will be captured by digital photography before and at 6 and 12 months after surgery by a high-volume retinal referral clinic (Calgary Retina Consultants) and images will be securely transferred to the University of Wisconsin Retina Core lab for analysis (Drs. [name]). In addition to the above data collection time points, patients will be given the option of extending their participation for an additional year, which will involve cardiac consultations, blood draws, and retinal imaging at 18- and 24-months post-surgery.

To complement this work, our collaborator, [name] (MD Anderson, Houston; **W**omen choos**I**ng **S**urgical **P**revention “**WISP**” trial [ClinicalTrials.gov Identifier: NCT02760849] researcher) will also provide plasma samples before and after PSO in their cohorts diagnosed with BRCA- or Lynch syndrome-associated mutations (~ 35 WISP participants).

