### Outcomes

The primary outcome is a change in levels of HSP27 following PSO. Plasma HSP27 will be measured using ELISA methods before and 1, 3, 6, and 12 months following surgery. Since previous findings have shown that higher HSP27 serum levels correlate with cardiovascular health [66], it is likely that women experiencing premature menopause after PSO will experience a worsening of their cardiovascular health (as measured by total cholesterol and LDL) and consequently, lower levels of HSP27. HSP27 localized to microparticles isolated from plasma and urine will also be measured using Western blotting and mass spectrometry. Additional primary outcomes assessed at the same time points and analyzed by ELISA are: HSP27 natural antibodies, which appear to be elevated in healthy controls compared to coronary artery disease patients, and PCSK9, which itself may be regulated by HSP27 (unpublished data). Secondary outcome variables are lipids (total cholesterol, triglycerides, HDL, LDL), ovarian hormones (estradiol, FSH, LH, progesterone), cytokines, and retinal vessel (arteriole and venule) diameters. Abnormally high lipid levels and/or severe post-menopausal symptoms following PSO may necessitate alterations in management and treatment by attending physicians.

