### Sample size calculation

To date, there are no prospective studies investigating HSP27, HSP27 Ab, and PCSK9 levels in women following PSO and the ensuing premature, surgical menopause. To estimate the necessary sample size, we assumed an effect size of 0.3, Type 1 error rate α = 0.05, and desired power = 0.90. Based on our conservative assumptions, a minimal sample size of at least 160 participants (40 per group) is needed for the study. Assuming 10% attrition rate over the course of the study, a minimum of 178 participants will be required (which is well below our recruitment target of 240). Once there is sufficient enrollment (*n* = 6 / group), effect size will be recalculated based on pilot data (again presuming α = 0.05 and power = 0.90) and the sample size adjusted accordingly as the study continues.

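### One unqualified p<0.05 rule covers every secondary marker, including a multi-analyte cytokine array, with no testing order, false-discovery control or exploratory label among the secondaries

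*Protocol article*

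**What the plan says.** Statistical analyses gives one decision rule, "Probability (p) of less than 0.05 will be considered significant", and does not restrict it to any outcome. For continuous variables, "the variance between the groups will be analyzed using ANOVA".

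Outcomes makes HSP27 the primary outcome, adds HSP27 antibodies and PCSK9 as further primaries, and then states: "Secondary outcome variables are lipids (total cholesterol, triglycerides, HDL, LDL), ovarian hormones (estradiol, FSH, LH, progesterone), cytokines, and retinal vessel (arteriole and venule) diameters". Data collection shows that the cytokine results come from a panel, listing among the uses of stored plasma "as well as inflammatory cytokine arrays". The number of analytes is not given. Blood is drawn before surgery and at 1, 3, 6 and 12 months; retinal images are taken before surgery and at 6 and 12 months.

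The Background states the aim as to "investigate whether PSO leads to increased cardiovascular risk as assessed by the measurement of conventional and novel surrogate markers for CAD". The Abstract describes the primary endpoints differently from Outcomes: its list includes the hormone profile, the lipid profile and the inflammatory cytokines.

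**The concern.** The article does more than leave multiplicity unmentioned. It fixes a rule, and as written the rule makes any secondary result below 0.05 significant. The secondaries are numerous and have no testing order, no error control and no exploratory label. LDL and total cholesterol have a predicted direction (Study design, Outcomes, Discussion). No named cytokine does, so a difference in any analyte, in either direction, would qualify.

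The study judges cardiovascular risk through its markers, and the Discussion looks ahead to larger studies and to using the markers as predictors. A chance result in the array could therefore be taken forward as a candidate risk marker. The secondary label gives limited protection while the Abstract calls several of the same variables primary.

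**Working it through.** **The plan's own figure.** Sample size calculation says "we assumed an effect size of 0.3, Type 1 error rate α = 0.05, and desired power = 0.90" and concludes that "a minimal sample size of at least 160 participants (40 per group) is needed for the study". The type of effect size is not stated. Read as Cohen's f in a four-group one-way ANOVA:
- Noncentrality = N × f² = 160 × 0.3² = 14.4, with 3 and 156 degrees of freedom.
- Power at 0.05 = 0.897, against the stated 0.90. With 41 per group (164) it is 0.905.
- Attrition: 160 / 0.9 = 177.8, rounded up to 178, which matches "Assuming 10% attrition rate over the course of the study, a minimum of 178 participants will be required".

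The calculation reproduces, and it is for one test at 0.05. It makes no allowance for further tests.

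**Formulas.** For m independent null tests at 0.05, the chance of at least one false positive is 1 − 0.95^m. The expected number of false positives is 0.05 × m, whatever the correlation. For correlated outcomes I simulated m equicorrelated null four-group tests in the large-sample form (chi-square, 3 degrees of freedom).

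**Lipids and retinal diameters.** Hormones are left out because removing functioning ovaries is expected to change them.

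| Tests counted | m | Correlation 0 | 0.3 | 0.5 | 0.8 |
|---|---|---|---|---|---|
| 4 lipids + 2 diameters, one test each | 6 | 0.26 | 0.24 | 0.22 | 0.14 |
| Each visit: 4×4 + 2×2 | 20 | 0.64 | 0.55 | 0.43 | 0.24 |

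Check of the independent values: 1 − 0.95^6 = 0.265; 1 − 0.95^20 = 0.642.

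**A smaller null set.** The protocol expects LDL and total cholesterol to rise, so they may not be null. Removing both leaves 2×4 + 2×2 = 12 tests by visit: 1 − 0.95^12 = 0.46 if independent. With one test for each of the four remaining variables, 1 − 0.95^4 = 0.19.

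**Cytokine array.** The analyte count is an assumption, shown as a range.

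| Assumed analytes | Expected false positives, one visit | Expected, four visits |
|---|---|---|
| 10 | 0.05 × 10 = 0.5 | 2 |
| 20 | 0.05 × 20 = 1 | 4 |
| 40 | 0.05 × 40 = 2 | 8 |

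**The case against.** The strongest reply is that error control for secondary outcomes in an observational pilot is usually left to the analysis plan or full protocol, neither of which is shown, and that a short article section giving a generic threshold contradicts nothing. Part of this stands. Had the article been silent there would be little to raise, and an unseen plan may narrow the rule. But the article states a rule whose wording reaches every outcome, and that wording can be corrected where it stands.

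Other objections limit the point:
- A reader might infer that the plan has no hierarchy at all. It has one: Outcomes puts HSP27 and two further markers above the rest. What is absent is any order or control within the secondaries.
- A reader might infer that chance findings will be reported as proof of raised cardiovascular risk. The text does not say that one isolated secondary result would support the hypothesis. It calls the work a pilot, and a four-group F test has no direction. Only the weaker statement holds: such results could be carried forward.
- Visit-by-visit testing is not clearly specified. Means are given for each time point, but the ANOVA is described only as between groups. Nor does the article say that each analyte is declared significant separately.
- A null of equal levels in all four groups is doubtful for some markers, since one group is post-menopausal.

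The pilot framing does not remove the problem. Screening for candidate markers is where false-discovery control or an exploratory label is most useful, and calling every marker significant at 0.05 is not exploratory reporting.

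**Conclusion.** The point holds in limited form. As written, the significance rule covers all secondary markers without order, adjustment or exploratory label, and the Abstract and Outcomes disagree on which markers are primary.

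On the most restrained count, one test for each of six lipid and retinal variables, the chance of at least one false positive is 0.26 if independent and about 0.14 at correlation 0.8, against a nominal 0.05. That figure needs no assumption about visits or array size, but it does assume that all six variables are null. The larger figures are conditional: 0.24 to 0.64 requires a test at every visit, and the array's expected count depends on an analyte number that the article does not give. It would be too strong to say that a false positive is probable on the lipid and retinal markers alone, because even with visit-by-visit testing the chance at correlation 0.5 is 0.43.

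This is a cheap improvement, not a flaw that undermines the primary comparison.

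**What to change.** In Statistical analyses:
1. Confine the claim of significance at p<0.05 to the primary outcome or outcomes.
2. Analyse the cytokine array as one exploratory family, with Benjamini-Hochberg adjusted values across all analytes and visits tested. State the number of analytes.
3. Label the lipids and retinal diameters exploratory and report them as estimates with 95% intervals. LDL and total cholesterol can be marked as having a predicted direction. LDL need not be made conditional on a significant primary result: with three primaries such a gate is undefined, and it could block the marker with prior support.
4. Treat the hormones as confirmation of the endocrine effect of surgery, not as evidence on cardiovascular risk.

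Also reconcile the Abstract with Outcomes on which markers are primary.

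The cost is a few sentences, with no added samples, visits or participants. The downside is that fewer secondary results can be called significant, and modest cytokine changes may not pass the false-discovery threshold.

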#### PCSK9

Interest in PCSK9 arose in 2003 when a gain-of-function *PCSK9* mutation was linked with autosomal dominant hypercholesterolemia [75]. This was subsequently confirmed when loss-of-function mutations in PCSK9 were shown to lower LDL [76]. Later experiments indicated that PCSK9 interferes with clearance of LDL from the circulation by binding to LDL-receptor (LDL-R) and facilitating its degradation [77]. Higher circulating plasma levels of PCSK9 has been shown to positively correlate with plasma levels of LDL and susceptibility to CAD; individuals with a PCSK9 loss of function display reduced LDL levels and lower risk of CAD [78]. Findings from the Dallas Heart Study suggest that PCSK9 levels are higher in post- menopausal compared to pre-menopausal women [79]. Of note, our laboratory obtained promising in vitro and in vivo results supporting the role of recombinant HSP27 in reducing PCSK9 levels in both liver cells / tissue and serum (unpublished data).

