#### Retinal vessel analysis

With advances in technology, relatively low cost, excellent reproducibility and radiation free testing, assessment of retinal arterioles is an attractive screening modality for assessing CAD risk [80–84]. Recently, changes in retinal microvessels were reported to correlate with cardiovascular outcomes [85]. Narrower retinal arterioles and wider retinal venules were associated with increased long-term risk of cardiovascular mortality and ischemic stroke both in male and female patients. Measurements of the central retinal arteriolar equivalent (CRAE) and the central retinal venular equivalent (CRVE) were also linked to cardiovascular disease, and in women were predictive of stroke [85]. Hence, retinal arteriolar narrowing is an early marker of systemic microvascular dysfunction with a higher sex-specific risk predictability for atherosclerotic disease in women [85]. Studies are ongoing to determine if retinal vessel parameters are static or can improve with cardiovascular risk factor modification (e.g., ClinicalTrials.gov identifiers: NCT02853747 and NCT02796976) [86]. Therefore, we are using retinal vessel analysis as a surrogate CAD endpoint as it has previously been indicated to be predictive of atherosclerotic events (i.e., small arteriole: large venule diameter ratio) [85].

This study will address the hypothesis that PSO intervention in pre-menopausal women, which causes an abrupt drop in estrogen and premature menopause, leads to physiological changes that increase cardiovascular risk. Surrogate markers for CAD (conventional and novel biomarkers, as well as measurement of an emerging physiological parameter reflective of CAD – retinal vessel analysis) will be used as tools to evaluate cardiovascular risk, with the long-term goal of potentially using these markers as predictive determinants of cardiovascular health in other at-risk populations.

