### Participant recruitment

Depending on family history and outcome of genetic testing, women that are positive for mutations in BRCA1/2 or Lynch syndrome associated-genes (e.g., HNPCC) may be referred by the University of Calgary’s team of genetic counselors for an information sharing consultation with gynecologists who specialize in minimally invasive PSO. During the medical genetics consultation, patients will be given a cursory introduction to this study via dissemination of an information pamphlet. After discussing with their gynecologist, who will further elaborate on the details of this study, patients who decide to undergo PSO and are interested in participating will then be scheduled for an appointment with a cardiologist ([name]). Post-menopausal women considering PSO and pre-menopausal women undergoing other pelvic surgeries will be introduced to the study by the same team of medical genetics counsellors and gynecologists, while non-surgical control participants will be enrolled through the use of recruitment flyers posted at the University of Calgary and its affiliated hospitals. Active patient enrollment for this study will take place over 3 years. Recruitment targets for each of the four patient treatment groups are 20 per year, totalling 240 participants for the duration of the study.

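### The four-group ANOVA does not isolate PSO in pre-menopausal women; the contrast with the pre-menopausal controls should be named as the primary comparison

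*Protocol article*

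**What the plan says.** The Statistical analyses section summarises continuous outcomes by mean and standard deviation at each time point and states that "the variance between the groups will be analyzed using ANOVA", with significance at p below 0.05. It names no contrast and no group-by-time term, and does not say whether levels or changes are compared. It adds regression to examine relationships between variables.

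Under Sample size calculation, "we assumed an effect size of 0.3, Type 1 error rate α = 0.05, and desired power = 0.90", and the result is that "a minimal sample size of at least 160 participants (40 per group) is needed for the study". The four groups are (i) pre-menopausal PSO, (ii) post-menopausal PSO, (iii) pre-menopausal women having other pelvic surgery and (iv) pre-menopausal women without surgery.

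The hypothesis, at the end of the Retinal vessel analysis section, is that "PSO intervention in pre-menopausal women, which causes an abrupt drop in estrogen and premature menopause, leads to physiological changes that increase cardiovascular risk". The Outcomes section makes the change in HSP27 after PSO the primary outcome, and adds HSP27 antibodies and PCSK9 as further primary outcomes. The Study design section gives each comparator a role: group ii tests removal of non-cycling ovaries without an estrogen drop, group iii controls for pelvic surgery, and group iv is the non-surgical reference for both pre-menopausal surgical groups. On PCSK9, the Background says that cited findings suggest "PCSK9 levels are higher in post- menopausal compared to pre-menopausal women".

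**The concern.** The scientific question concerns one group against specific comparators. A four-group F test asks only whether any of the four means differ. One of the four groups is already post-menopausal at entry, so it may differ from the other three for reasons unrelated to surgery. A significant F test would then not support the claim about PSO. At stake is the reading of the main result, most plainly for PCSK9, where the article itself points to a menopausal difference. The sample size rests on the same test, so the study is not explicitly sized for the comparison it was set up to make.

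**Working it through.** **1. Reproducing the stated sample size.** Inputs from Sample size calculation: effect size 0.3, alpha 0.05, power 0.90, four equal groups. The type of effect size is not named. Reading it as Cohen's f in a one-way ANOVA, the test is a noncentral F with 3 and N − 4 degrees of freedom and λ = N·f².

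- At N = 160, λ = 160 × 0.09 = 14.4 and power is 0.897.
- The first equal-group N to reach 0.90 is 164 (41 per group, power 0.905). The stated 160 agrees within rounding.
- Attrition: 160 / 0.90 = 177.8, so 178, as stated.
- Readings that do not reproduce 160: f = 0.3 with two groups (N = 120) or three groups (N = 144), and a two-mean comparison with d = 0.3 (234 per group).

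The word omnibus does not appear in the article, but this is the reading that fits its number.

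**2. What f = 0.3 means for one group.** If one of four equal groups is shifted by d SD, f = d·√3/4, so f = 0.3 corresponds to d = 0.3 × 4/√3 = 0.69. The F test does not care which group is shifted. Its power of 0.897 at 40 per group applies equally when group i differs and when only group ii differs.

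**3. No PSO effect, group ii shifted in level.** The article gives no size for the menopausal difference, so d is an assumption, shown over a range. λ = N × 3d²/16. The sample sizes are 40 per group (the stated minimum) and 60 per group (240 / 4, the full target).

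| Assumed shift in group ii | λ at 40 / 60 per group | P(F test significant), 40 per group | P(F test significant), 60 per group |
|---|---|---|---|
| 0.3 SD | 2.70 / 4.05 | 0.24 | 0.36 |
| 0.5 SD | 7.50 / 11.25 | 0.61 | 0.81 |
| 0.8 SD | 19.2 / 28.8 | 0.97 | 0.997 |

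These apply to a comparison of levels at a single visit, including the one before surgery.

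**4. The same scenario analysed in other ways** (simulation, 10,000 runs per setting, assumed correlation of 0.6 between baseline and follow-up):

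- Contrast of group i with the mean of groups iii and iv, on levels: rejection about 0.05 throughout.
- Four-group F test on change from baseline: rejection about 0.05 throughout, because a stable level difference cancels.

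**5. Power when only group i differs, by 0.69 SD of the analysed variable.** Two-sided alpha 0.05, error pooled over four groups. The noncentrality is d / √(Σc²/n).

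- Group i versus iii and iv combined, n = 40: Σc² = 1 + 0.25 + 0.25 = 1.5, so 0.693 / √(1.5/40) = 3.58 and power is 0.945.
- Group i versus iii alone, n = 40: 0.693 / √(2/40) = 3.10 and power is about 0.87.
- Group i versus iii alone, n = 54 (240 less 10%, divided by four): 0.693 / √(2/54) = 3.60 and power is about 0.95.
- Four-group F test, n = 40: power 0.897.

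**The case against.** The strongest reply is that the article does describe the right comparisons. The Study design section gives every comparator its purpose, an ANOVA commonly comes with planned contrasts, and a journal article may leave those to a full protocol or SAP that is not shown. That is fair as far as it goes, and the absence of contrast detail would not by itself be a point. But the article fixes a test and a sample size, and both fit the four-group question rather than the comparisons that it describes.

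Some stronger readings are tempting and are not supported:

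- **That the F test will be falsely significant at every visit.** This needs levels to be analysed. Reporting means by time point points that way, but the primary outcome is defined as a change and the ANOVA sentence does not settle which is meant. On change from baseline, a stable menopausal difference does no harm.
- **That the article establishes a large menopausal difference.** It says only that findings suggest one for PCSK9, without a size, and reports none for HSP27, the lead primary outcome. Estradiol and FSH would be expected to differ, but the Outcomes section makes them secondary.
- **That any specific contrast beats the F test on power.** Only the pooled contrast does in the scenario above. Group i against the surgical controls alone has slightly less power at 40 per group (about 0.87 against 0.897).

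**Conclusion.** The point holds in this form: the stated between-group test, and the sample size that fits it, do not answer the question set by the hypothesis, the primary outcome and the comparator roles. This is true whether levels or changes are analysed, since a four-group F test does not single out pre-menopausal PSO in either case.

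The spurious-significance figures are conditional. They assume that levels are compared, that PSO has no effect, and that group ii is shifted by an assumed 0.3 to 0.8 SD. The low end of that range is modest and the high end near certainty. They bear chiefly on PCSK9 and the hormones, not on HSP27 as far as the article reports. The power gain of the pooled contrast over the F test, about 5 percentage points at 40 per group (0.945 − 0.897 = 0.048), assumes that group i alone differs, by 0.69 SD.

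**What to change.** In Statistical analyses, name the planned contrast of group i against groups iii and iv combined, on change from baseline or with adjustment for baseline, as the primary comparison. Keep group i versus iii and group i versus iv as supportive contrasts, so that the reader can see whether the surgical and non-surgical controls agree. Report the change in group ii separately, as the check on removing non-cycling ovaries that Study design intends. State that the omnibus p-value will not be used to support the PSO claim.

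In Sample size calculation, say what the effect size of 0.3 refers to and restate the basis for the named contrast. The recalculation from pilot data planned there should use the same contrast.

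The cost is wording in two sections and one recalculation. No new data are needed and, in the scenario above, no participants beyond the 240 target.

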## Methods / design

### Study design

This is a single-center, prospective, cross-sectional study which addresses whether women undergoing PSO develop features of cardiovascular disease as assessed by conventional (e.g., cholesterol) and novel biomarkers, including HSP27. Candidates for surgery will be introduced to the study by medical genetics counselors and gynecologists specializing in minimally invasive PSO (University of Calgary’s affiliated hospitals, Calgary, Alberta). Patients who decide to undergo surgery and are interested in participating in this study are then scheduled for a cardiac consultation with [name] (University of Calgary). To determine if the sudden drop in estrogen following PSO leads to increases in cardiovascular disease markers, the study population will involve women representing the following four different treatment groups:*Pre-menopausal women undergoing PSO.* This patient group is predicted to develop the most obvious changes in cardiovascular disease markers, as previously indicated by increases in total cholesterol and LDL levels [59, 60] – this is most likely attributed to the abrupt loss in estrogen after surgical removal of functional ovaries.*Post-menopausal women undergoing PSO.* Comparison with this group of women will address whether the surgical removal of ovaries alone (which are non-cycling), and not the sudden drop in estrogen per se, contributes to increases in cardiovascular disease markers.*Pre-menopausal women experiencing other pelvic surgeries* that spare both ovaries and fallopian tubes (e.g., hysterectomy, salpingectomy). This “surgical control” group is included to eliminate the possibility that surgical interventions in the pelvic region affect levels of cardiovascular disease markers over time.*Pre-menopausal women, no surgery.* It is expected that women in this non-surgical, pre-menopausal control group will not exhibit remarkable changes in cardiovascular disease markers during the study’s time frame, and as such, will be used to compare with both groups of pre-menopausal women having undergone surgery (PSO or other pelvic surgery).

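### The group comparison is an unadjusted ANOVA by time point, not tied to change from baseline, and multivariable regression is triggered by the results, so confounding can bias the main contrast

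*Protocol article*

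**What the plan says.** All references are to the protocol article.

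- **Outcomes.** "The primary outcome is a change in levels of HSP27 following PSO". Plasma HSP27 is measured before surgery and at 1, 3, 6 and 12 months. HSP27 antibodies and PCSK9 are additional primary outcomes at the same times; lipids are secondary.
- **Statistical analyses, group comparison.** "Experimental outcomes for continuous variables will be expressed as means ± standard deviation for each time point and the variance between the groups" is the wording for the summaries, and "the variance between the groups will be analyzed using ANOVA". No covariate, baseline value or change score is mentioned.
- **Statistical analyses, regression.** "In order to examine the relationship between variables, regression analysis will be performed". The next sentence is: "If more than one predictor variable is found to affect the outcome, multivariate regression will be employed to identify significant associations".
- **Participant recruitment.** Women having PSO before menopause are referred through genetic counsellors and gynaecologists. Post-menopausal PSO candidates and women having other pelvic surgery "will be introduced to the study by the same team of medical genetics counsellors and gynecologists". For the fourth group, "non-surgical control participants will be enrolled through the use of recruitment flyers posted at the University of Calgary and its affiliated hospitals".
- **Study design.** The other-pelvic-surgery group "is included to eliminate the possibility that surgical interventions in the pelvic region affect levels of cardiovascular disease markers over time". The no-surgery group is the comparator for both pre-menopausal surgical groups. The stated exclusions are pre-existing malignancy and a myocardial infarction in the year before surgery. The baseline cardiac consultation records, among other things, medication use, hypertension, diabetes and prior cardiovascular events.

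**The concern.** Group membership here is decided by mutation status, clinical indication, menopausal status and volunteering, not by chance. The contrast between pre-menopausal PSO women and their controls can be read as an effect of ovarian removal only if the groups are comparable at baseline or the analysis makes them so. The section that fixes the analysis does neither. It sets an ANOVA without covariates, does not say that the analysed quantity is change, and lets a multivariable model in only after predictors have been seen to matter in these data.

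Two harms follow. Baseline differences in age, medication or risk factors can appear as, or hide, an effect of PSO. And the choice of final model depends on the results. With 40 to 60 women per group, a genuine confounder can easily fail to show a clear association and be left out. The article itself gives grounds for taking age and menopausal stage seriously: its Background reports raised cardiovascular risk particularly when surgery takes place before 45, and higher PCSK9 after menopause.

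**Working it through.** **1. Is the planned comparison unadjusted?** Two things point the same way.

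- The text: ANOVA is named, and no covariate is listed.
- The sample size. Inputs from Sample size calculation: effect size 0.3, α = 0.05, power 0.90, four groups. Reading 0.3 as Cohen's f in a one-way ANOVA, the noncentrality is λ = f² × N.
  - At N = 160: λ = 0.09 × 160 = 14.4 and power = 0.897.
  - At N = 164 (41 per group): λ = 14.76 and power = 0.905.
  - The stated 160 is thus reproduced to within one woman per group. The attrition step, 160 / 0.90 = 177.8, gives the stated 178.
  - Reading 0.3 as a two-group standardised difference would need 234 per group and does not fit.

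  So the sizing also matches a four-group comparison without covariates.

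**2. Is it tied to change?** Set side by side, Outcomes defines change in HSP27, while Statistical analyses describes summaries at each time point and a between-group ANOVA. Nothing connects the two.

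**3. When do several covariates enter together?** Simple regression is planned unconditionally, but to examine relationships between variables. Only the multivariable step is conditional, on more than one predictor being found to matter. Neither step is described as adjusting the group contrast.

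**4. What could an offset do? (illustration)** The article gives no baseline imbalance and no association between covariates and markers, so the offset δ below is an assumption. It is the difference between two groups that remains when PSO has no effect, in SD of the analysed quantity.

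- Women per group: the target of 20 per year over 3 years gives 60; less 10% attrition, 60 × 0.9 = 54.
- Two-sided t test at 5%: df = 2 × 54 − 2 = 106, critical value 1.983, noncentrality δ × √(54/2).
- Four-group ANOVA with one group shifted by δ: f = δ × √3 / 4, λ = f² × 216.

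| Assumed offset δ (SD) | t-test noncentrality | False-positive rate, two groups | λ (ANOVA) | False-positive rate, ANOVA |
|---|---|---|---|---|
| 0.1 | 0.520 | 8.1% | 0.405 | 7.4% |
| 0.2 | 1.039 | 17.8% | 1.620 | 16.0% |
| 0.3 | 1.559 | 33.9% | 3.645 | 32.3% |

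The omnibus test gives nearly the same picture as the pairwise one. Recruiting more women does not help: at δ = 0.2 the pairwise rate is 14.3% with 40 per group and 19.2% with 60, because a fixed bias is detected more often as precision rises.

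**The case against.** The strongest reply is that the primary outcome is a change within each woman. If change is what is analysed, stable level differences due to age, adiposity or smoking cancel. This stands as far as it goes, and it limits how large δ is likely to be. It does not settle the matter: the analysis section never says that the ANOVA is on change, and change scores do not remove differences in trajectory linked to age, nearness to menopause or medication.

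Several stronger readings are tempting and are not supported:

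- *Regression is used only when predictors are significant.* Regression itself is planned without condition; only its multivariable extension is conditional, and no p-value rule for entry is stated.
- *Every group comes by a different route.* The three surgical groups are introduced through genetic counsellors and gynaecologists. Only the no-surgery group comes by flyer, and the flyers are posted at affiliated hospitals as well as the university.
- *Neither control group can do its job.* The aim of eliminating an alternative explanation is stated only for the surgical controls, and concerns markers over time.
- *Age is shown to drive the primary markers.* The article does not link age to HSP27, its antibodies or PCSK9 among pre-menopausal women.

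It is also fair that this is a condensed article describing pilot work, and that a covariate list or matching details may sit in a fuller document. The point does not rest on their absence. It rests on the method and the conditional rule that the article does state, which a later list of fixed covariates would have to replace.

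**Conclusion.** The point holds in this form: for a non-randomised four-group comparison, the article sets an unadjusted ANOVA by time point, leaves it unconnected to the change outcome, and makes multivariable regression depend on what the data show. Followed as written, this can leave confounding in the contrast between pre-menopausal PSO women and their controls.

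The size of the bias is unknown. A reader might take 8% to 34% as the study's real error rate; it is not. Those figures apply only if a residual offset of 0.1 to 0.3 SD exists between two groups of 54, and the documents neither give nor exclude such an offset. If change is analysed, the offset that matters is in change, which may be smaller than a difference in levels. The contrast with post-menopausal PSO women is a separate limit: those women differ in menopausal status by design and so very probably in age, and no adjustment can separate the two.

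**What to change.** Replace the conditional sentence with a stated primary model:

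- **Outcome:** change in HSP27, with the same model for HSP27 antibodies and PCSK9.
- **Adjustment:** the woman's own pre-surgery marker value (the baseline sample for no-surgery controls), age, and baseline medication use, hypertension and diabetes, all kept whatever their p-values. Add BMI and smoking if the cardiac consultation records them; the article does not name either.
- **Post-menopausal PSO group:** state that this contrast cannot separate age from menopausal status, and interpret the group mainly by within-woman change.
- **Regression on other predictors:** keep it, labelled exploratory.

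The cost is a change of wording and a few degrees of freedom. Age, medication, hypertension and diabetes need no new tests. Matching controls to pre-menopausal PSO women in age bands is an optional addition; it would slow control recruitment somewhat and has to be decided before those controls are enrolled. Baseline adjustment will not deal with treatment changes after surgery, which the Outcomes section anticipates, so these should be reported by group.
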